### Outcome Measures and Data Collection

#### Primary Outcome Variables

Two major variables will be computed to investigate the effect of these two gait training programs intended to develop gait adaptability behavior in older adults. In terms of gait adaptability behavior, gait parameters will be computed from an innovative gait adaptability test. In the context of fall prevention, this specific test will allow us to investigate gait adaptability behavior with several levels of analysis. In terms of VR-HMD acceptance, we will examine acceptance before and after the use of the VR device designed to prevent falls in older adults. We will determine attitudes and representations toward the technology device used in this training program to ensure that older adults accept the VR-HMD.

#### Gait Adaptability Test

Gait adaptability capacities will be assessed by a specific gait test created to assess gait parameters during goal-directed tasks. Feet positions will be measured by a 7-m-long portable pressure-sensitive walkway, GaitRite (CIR Systems, Inc), in the real world. The security system (safety harness connected to an in-ceiling rail by a lanyard) will also be used to carry out the tests. First, participants will be instructed to walk at a normal pace on the walkway. The average preferred gait speed, step length, and step duration (with their variabilities) will be calculated over 6 trials. Afterward, physical obstacles will be placed on the walkway. Participants will perform 3 different locomotor tasks: simple locomotor pointing, crossing-over, and stepping-over tasks (Figure 3). They will perform 10 trials of each goal-directed task. Participants will be instructed to negotiate obstacles as quickly as possible without colliding with them. The size of the obstacles will be proportional to the anthropometric data of the participants (ie, based on individual leg length).

For the locomotor pointing task, participants will be instructed to place the right foot tip as close as possible to the lower extremity of the target. The pointing performance (ie, the horizontal distance between the tip and the lower extremity of the target) will be measured. For the crossing-over task, participants will be instructed to cross an obstacle with a depth of 60% of their leg length. The crossing performance (ie, the horizontal distance between the tip and the lower and upper extremities of the target) will be measured. For the stepping-over task, participants will be instructed to step over an obstacle with a height of 20% of their leg length. The stepping performance (ie, the vertical distance between the tip and the target) will be measured using Kinovea Video analysis software (version 0.8.15; 2006-2011 Joan Charmant and Contrib). The position of obstacles will be manipulated (3 different positions each separated by 30 cm intervals) and presented in a randomized order (2 trials for each position condition) to avoid locomotor regularities and prevent any calibration of the distance being covered. Finally, participants will perform 10 trials of a mixed condition: a combination of 2 previous goal-directed tasks (Figure 3).

By recording successive feet positions in relation to the obstacles, gait adaptability behavior will be analyzed through intertrials and trial-by-trial analyses [44,51,72].

In the intertrial analyses, the SD of the toe-obstacle distances and the SD of the step lengths will be measured. If the locomotion behavior produced is functional, the intertrial analysis should reveal inverted patterns of variability [44,51]. This result reveals that step length adjustments are produced to minimize toe-obstacle distance at the last footfall and thus perform optimal foot positioning. We hypothesize that the training carried out should accentuate the presence of compensatory variability (pre- vs posttest comparison) but also that the compensatory variability produced following the training should be more pronounced for the VR group than for the NW group.

The trial-by-trial analysis makes it possible to identify precisely for each trial the presence of adjustments of the step lengths and their distribution throughout the trial by comparing each step length with the average pattern of step length (see the study by Montagne et al [72] for a similar procedure). The second part of the analysis consists in computing for each step the number of adjustments needed to place the foot on the target and the number of adjustments actually implemented [44,72]. Here again, we hypothesized that the training carried out should enable participants to improve their ability to produce adaptive behavior. More precisely, not only should step length adjustments be initiated sooner after training (ie, after the test) so that they can be spread over a larger number of steps but also the adjustments produced should more accurately reflect the adjustments required to succeed in the task. These improvements in adaptive locomotor skills should be more pronounced for the VR group.

To sum up, from this gait adaptability test, we will characterize the gait adaptability behavior with different levels of analysis. In addition to a traditional analysis of locomotion (ie, performance, mean step length and associated variability, and mean walking speed and associated variability), further levels of analyses (ie, intertrial and trial-by-trial analyses) will investigate the onset of the regulation, the regulation strategy, the relationship between needed and produced regulations over the obstacle approach, and the strength of the perceptual motor coupling. Our hypothesis was that the combination of traditional measures and these new measures should provide a more integrated understanding of the improvements caused by the implementation of VR training protocols. While traditional measurements are focused on the behavior of the older adult, the new measurements make it possible to analyze their behavior in relation to the environment. We believe that the joint use of these levels of analysis allows a finer characterization of product behavior and its evolution.

Finally, in the mixed condition, a gait adaptability score will be calculated based on gait performance and speed. The gait adaptability score is calculated from the pointing, crossing, and stepping performances modulated by the gait speed. The score is the product of gait performance and velocity so that it accounts for the capacity of older adults to manage the speed-accuracy conflict in the context of producing a goal-directed locomotor displacement. The performance obtained is the sum of the performance achieved in the two tasks. In the pointing task, performance is higher the closer the foot is to the mark (a score of 10 when the tip of the foot is <10 cm from the edge of the target, 8 between 10 and 15 cm, etc). In stepping-over tasks, performance is maximum (a score of 10) when the task is carried out in accordance with the instructions (ie, without meeting the obstacle), while imperfect completion of the task gives rise to a score of 5. The same methodology is applied during the crossing task. The sum of the performances achieved gives rise to an overall performance for each trial (maximum 20) that will be weighted by the average walking speed to complete the route (eg, 20×0.90=18).

#### VR-HMD Acceptance

For the VR group only, VR-HMD acceptance before and after use will be assessed using the TAM. According to this model, intention to use a technology is positively predicted by its perceived usefulness and its perceived ease of use. VR-HMD acceptance will be assessed through 4 variables: perceived usefulness, perceived ease of use, perceived enjoyment, and intention to use [54,73,74]. Participants will answer the 3 items per variable on a Likert scale from 1 (strongly disagree) to 10 (strongly agree): perceived usefulness (eg, “I believe using VR hardware would help me be more effective in my locomotion”), perceived ease of use (eg, “I believe using VR hardware would be easy for me”), perceived enjoyment (eg, “I believe I would find using VR hardware enjoyable”), and intention to use (eg, “I intend to use VR hardware within the foreseeable future”). In older adults, the TAM has been recently used to study VR-HMD acceptance before [44,53] and after the use [44] of a device intended to prevent falls among older adults.

### Secondary Outcome Variables

As mentioned in the Introduction section, interactions exist among gait behavior, functional capacities, and psychological states. In addition to the study of gait adaptability behavior and VR-HMD acceptance, several secondary variables will be investigated to characterize potential functional capacities and psychological state changes over the gait training programs.

#### Functional Capacities

Mobility evaluation will be assessed with the Timed Up and Go test [75]. Participants must sit down on a chair with their feet on the floor and their hands on their legs. At the “go” signal, they will stand up, walk 3 m, turn around the cone, walk back, and sit down again. The performance time (in seconds) will start when the participant starts moving, and it will end when the participant sits down again. Two trials at a self-paced velocity and 2 as fast as possible will be performed. For analysis, the mean value of the 2 trials in each condition will be considered.

Balance evaluation will be assessed with the Unipedal stance test [76]. Participants must lift one of their legs (while looking at a mark placed in front of them at eye height) and keep a stable equilibrium. The performance time (in seconds) will end when participants lose equilibrium (with a maximum trial duration of 60 seconds). Three trials with eyes open and 3 with eyes closed will be performed. For analysis, the best value of the trials in each condition will be considered as recommended in the study by Springer et al [76].

#### Sample Size

The sample size calculation was performed using G*Power (version 3.1.9.7). To detect relevant within-between-group differences, we calculated a sample size sufficient to detect small effect sizes. On the basis of values generally observed in studies conducted in the field of acceptability and acceptance of technologies in general (because no study similar to ours has yet been conducted), f=0.2, α=.05, and *P*=.80 were chosen to favor clinically significant effect sizes [79]. To test the main hypotheses of this study, 50 participants are required. To compensate for possible dropouts, 5 more participants will be included in each group. The 2 groups will be composed of 30 participants each.

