**Methods:**

We will be conducting a randomized controlled trial with pretests, posttests, retention tests, and follow-up. In total, 40 healthy independent-living community dwellers (aged between 65 and 80 years) will be allocated, after a general medical examination, to the VR or the NW group for a training program of 6 weeks. Primary outcomes related to gait adaptability capacities (ie, analysis of adjustments made in different locomotor tasks) and acceptance of the VR device (ie, analysis of acceptance) will be assessed before and after the intervention and 1 month after the completion of the training program (retention). A follow-up will be done during the 12 months after the completion of the gait training program.

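### The article gives two enrolment totals (40 and 60), and the 50 completers said to serve the main hypotheses do not give 80% power at 40 enrolled or for the acceptance hypothesis, which is tested in the VR arm only

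*Protocol article*

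**What the plan says.** The abstract's Methods paragraph gives one total: "In total, 40 healthy independent-living community dwellers (aged between 65 and 80 years) will be allocated" to the two groups.

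The Sample Size section gives another. It describes a G*Power calculation for a within-between design: "To detect relevant within-between-group differences, we calculated a sample size sufficient to detect small effect sizes". The inputs are "f=0.2, α=.05, and *P*=.80 were chosen to favor clinically significant effect sizes", with the effect size drawn from studies of technology acceptance. The result is "To test the main hypotheses of this study, 50 participants are required", then 5 more per group for dropout, and finally "The 2 groups will be composed of 30 participants each".

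The abstract and the Primary Outcome Variables section treat gait adaptability and acceptance of the headset as the two primary outcomes. Objectives of the Study and Hypotheses makes a rise in acceptance hypothesis 4. The VR-HMD Acceptance section restricts who contributes to it: "For the VR group only, VR-HMD acceptance before and after use will be assessed using the TAM".

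The Statistical Analysis section keeps only participants who completed all pretests and posttests, and plans repeated measures ANOVA.

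**The concern.** Forty is neither the number enrolled (60) nor the number needed at analysis (50), so the two totals cannot both stand. If recruitment stopped at 40, the between-arm comparison of gait adaptability would lose the power the plan claims, and this cannot be repaired once enrolment has closed.

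The second problem remains at the full 60. One two-group calculation is offered for all the main hypotheses, but a group-by-time contrast does not exist for an outcome measured in one arm. Acceptance uses half the participants on whom the 80% rests, although its literature supplied the effect size.

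A lesser issue is that f=0.2 is called small without saying what difference between the arms it stands for.

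**Working it through.** **Inputs from the article.** f = 0.2, α = .05, power .80, two groups at 1:1, 50 evaluable, 60 enrolled, acceptance in the VR group only, completers analysed.

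**Inputs assumed.** The number of time points m and the correlation ρ used in the calculation are not stated. Data are collected at three times (T0, T1, T2), but the analysis section can be read as a pre/post comparison, so both m=2 and m=3 were tried, with sphericity.

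**Formula** (within-between interaction, noncentral F, k groups): λ = f²·N·m/(1−ρ), df1 = (k−1)(m−1), df2 = (N−k)(m−1). For one group, df1 = m−1 and df2 = (n−1)(m−1).

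**Step 1: reproduce the 50.**
- m=2, ρ=0.5: λ = 0.04×50×2/0.5 = 8.0, df 1 and 48, power 0.791. The first N to reach 80% is 52.
- m=3, ρ=0.4: λ = 0.04×50×3/0.6 = 10.0, df 2 and 96, power 0.802. The required N is exactly 50.

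So 50 is sound for the two-group interaction, and 50 + 2×5 = 60 follows.

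**Step 2: enrol 40 instead.** The plan's own retention is 50/60, and 40×50/60 ≈ 33 completers.

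| Evaluable N | m=2, ρ=0.5 | m=3, ρ=0.4 |
|---|---|---|
| 50 | 0.791 | 0.802 |
| 40 (no dropout) | 0.693 | 0.699 |
| 33 (plan's retention) | 0.605 | 0.605 |

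**Step 3: acceptance, VR group only, f=0.2.** Half of 50 is 25 completers. With m=2, ρ=0.5, λ = 0.04×25×2/0.5 = 4.0 on df 1 and 24.

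| VR completers | m=2, ρ=0.5 | m=3, ρ=0.4 |
|---|---|---|
| 30 (no dropout) | 0.563 | 0.561 |
| 25 | 0.484 | 0.478 |
| 20 (half of 40, no dropout) | 0.397 | 0.387 |

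For 80% power the VR group alone would need 52 or 50 completers. With 25, the detectable f is about 0.29 under either setting.

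**Step 4: what f=0.2 means between arms.** With two time points, the four interaction cell effects are ±0.2 SD, so the between-arm difference in change is 4×0.2 = 0.8 SD. Power for that difference with 50 completers depends on ρ: 0.716 at ρ=0.4, 0.791 at 0.5, 0.873 at 0.6. The difference detectable with 80% power runs from about 0.96 SD (ρ=0.3) to 0.63 SD (ρ=0.7). With three time points, the T0–T1 difference implied by f=0.2 depends on the pattern of means: 0.85 SD if T2 equals T1, 0.98 SD if T2 lies midway between T0 and T1.

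**The case against.** **The derivation already shows which total was meant.** The chain 50 + 2×5 = 60 is explicit, and the randomisation block size of 30 divides 60 but not 40. This makes 60 the likelier intention, and nothing shows that the trial will in fact recruit 40. Both totals are nevertheless current text and must agree.

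**Other inputs would rescue 40.** With three time points and ρ=0.5, power at 40 is 0.782 with no dropout. But those inputs would have required 42, not 50. A correlation high enough to bring 25 VR completers to 80% (about 0.8) is likewise incompatible with a stated 50. For the same reason, the 56% for acceptance at m=3, ρ=0.5 should not be quoted beside a requirement of 50.

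**The calculation never claimed to cover a one-arm test.** It is described as within-between, and an article may leave further justification to a full protocol. What stands against this is the article's own statement that 50 serves the main hypotheses, among which a primary outcome with a numbered hypothesis naturally belongs.

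**Hypothesis 4 is directional.** A one-sided paired test would have about 62% power, but the planned analysis is an ANOVA.

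**The small-effect label is a matter of wording.** This largely stands. The value f=0.2 is printed openly and the 50 reproduces. A reader might go further and infer that the trial can detect only a 0.8 SD difference, or that the authors would read a null result as excluding small effects. The first depends on the unstated time points and correlation, and nothing in the article says the second.

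**Conclusion.** The point holds on two counts. The contradiction between 40 and 60 needs no assumption. Under the two settings that reproduce about 50, enrolling 40 lowers power for the two-group interaction at f=0.2 to about 69–70% with no dropout and about 60% with the plan's own retention. Separately, hypothesis 4 rests on about 25 VR completers and has about 48% power at f=0.2 under the same settings.

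The percentages rest on assumed time points and correlation, on sphericity, and on applying the plan's f=0.2 to acceptance, which is where the plan took it from. A reader might infer that the 50 or the 60 is itself miscalculated. It is not: 0.791 against 0.80 is immaterial, and three time points with ρ=0.4 give 50 exactly. The wording of the effect size is secondary.

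**What to change.** 1. Change the abstract to 60 participants (30 per group, 50 expected completers).
2. In Sample Size, state the number of time points and the correlation used, and limit the 80% claim to the two-group group-by-time interaction at f=0.2.
3. Replace the description of the effect as small with the between-arm difference in change that f=0.2 implies under the authors' own inputs. It is 0.8 SD only with two time points, and the power for it depends on the correlation, so no fixed figure should be inserted before those inputs are known.
4. State that acceptance is tested in about 25 VR completers, with about 48% power at f=0.2 and a detectable f of about 0.29, recalculated if the authors' inputs differ from those assumed here.

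The cost is wording and a less favourable power statement. No extra participants are needed.

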#### Statistical Analysis

The statistical software JASP (version 0.17.1; 2023) will be used to run statistical analyses. The statistical level of significance was set at α=.05. Nonparametric tests were used when the distribution of the data was nonnormal. The statistical analysis will allow us to determine the effects of the two different training programs on the primary and secondary variables. The analysis will include participants who completed all the pretests and the posttests. Adherence to programs will be measured by the absence rate (in terms of %). Comparisons within and between groups before and after the intervention will be done using repeated measures ANOVA and Tukey tests as post hoc analyses. Effect sizes will be calculated using partial η^2^.

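### The primary gait outcome is a battery of roughly 12 to 40 variables, none of them named to decide hypothesis 2, so the risk of a false VR-superiority claim is well above nominal

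*Protocol article*

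**What the plan says.** The Primary Outcome Variables section announces that "Two major variables will be computed to investigate the effect of these two gait training programs": gait adaptability behavior and acceptance of the head-mounted display.

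The Gait Adaptability Test section then fills the first of these with a battery:
- unobstructed walking: speed, step length and step duration, each with its variability;
- three obstacle tasks analysed with traditional measures (performance, step length and walking speed, the last two with variability);
- intertrial measures (SD of toe-obstacle distance and SD of step length);
- further analyses that "will investigate the onset of the regulation, the regulation strategy, the relationship between needed and produced regulations over the obstacle approach", plus the strength of perceptual-motor coupling;
- a gait adaptability score from a mixed condition.

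Table 1 lists the whole test as the primary gait outcome. The same section predicts a VR advantage on several of these measures: compensatory variability, earlier onset and wider spread of adjustments, and closer agreement between produced and required adjustments.

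For the second variable, "VR-HMD acceptance will be assessed through 4 variables: perceived usefulness, perceived ease of use, perceived enjoyment, and intention to use". These are collected in the VR group only.

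On error control, Statistical Analysis states that "The statistical level of significance was set at α=.05" and specifies repeated measures ANOVA with Tukey post hoc tests. On size, the Sample Size section says that "f=0.2, α=.05, and *P*=.80 were chosen to favor clinically significant effect sizes" and that "To test the main hypotheses of this study, 50 participants are required".

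On timing, the Objectives and Statistical Analysis sections both describe a before-versus-after comparison. Table 1 places the primary outcomes at T0, T1 and T2. The summary text just above it places them at T1, T2 and T3.

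**The concern.** Hypothesis 2 concerns gait adaptability as a whole, but the analysis produces a separate ANOVA result for each gait variable, each judged at 5%. Tukey's procedure adjusts the pairwise comparisons of cells within one ANOVA. It does nothing across ANOVAs on different outcomes. The plan as written therefore lets hypothesis 2 be declared on any variable that reaches significance, and it gives no reading for a mixed pattern, such as VR better on onset of regulation and Nordic walking better on stepping performance.

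The stakes are high because the article's Conclusions say that confirming hypothesis 2 should establish VR as the more promising fall-prevention tool. That claim would rest on a comparison chosen after the data are seen.

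The sample size points the same way. It uses a single effect size and a single unadjusted 5% level, with the effect size based on "values generally observed in studies conducted in the field of acceptability and acceptance of technologies in general" and not on any gait variable. It is sized as if one test decided the matter, while the outcome section defines many.

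**Working it through.** **1. The plan's own sample size.** Inputs from Sample Size: f = 0.2, α = .05, power .80 (printed as P), and the aim stated as "To detect relevant within-between-group differences, we calculated a sample size sufficient to detect small effect sizes". The number of measurements m and their correlation ρ are not given; assume m = 2 and ρ = 0.5. For a group-by-time interaction with two groups, λ = f²·N·m/(1−ρ), with 1 and N−2 degrees of freedom.
- N = 50: λ = 0.04 × 50 × 2/0.5 = 8.0, power 0.79.
- N = 52: λ = 8.32, power 0.81.

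The stated 50 is thus reproduced closely, as one test at an unadjusted 5%. It depends on the unstated inputs: m = 3, ρ = 0.5 needs 42; m = 2, ρ = 0.3 needs 72.

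**2. Counting the gait variables.** The documents give no count, so this is a reconstruction.
- Per obstacle task: 5 traditional + 2 intertrial + 4 trial-by-trial (onset, strategy, needed versus produced regulation, coupling strength) = 11.
- Upper count, split by task: 6 unobstructed + 3 × 11 + 1 mixed score = 40.
- Lower count, each kind once: 11 + 1 mixed score = 12. The unobstructed measures are not counted again.

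**3. Chance of a false VR-favouring result.** With no true difference, a two-sided 5% test favours VR wrongly with probability 0.025. For k independent tests the chance of at least one is 1 − 0.975^k:
- k = 12: 1 − 0.975^12 = 0.26.
- k = 40: 1 − 0.975^40 = 0.64.

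For equal pairwise correlation r, the chance is that the largest of k equicorrelated standard normals exceeds 1.96 (numerical integration or simulation):

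| Variables | r = 0 | r = 0.5 | r = 0.7 |
|---|---|---|---|
| 12 | 26% | 16% | 12% |
| 40 | 64% | 29% | 19% |

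At r = 0.9, 40 variables still give 9%.

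For a false difference in either direction the figures are larger: 1 − 0.95^12 = 46% and 1 − 0.95^40 = 87% if independent, and 57% for 40 variables at r = 0.5. They are not the right measure of a false VR-superiority claim.

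**4. What the alternatives cost (m = 2, ρ = 0.5).**
- One named endpoint: 5% two-sided, 2.5% favouring VR; the stated N of about 50 stands.
- Four co-primary variables with Bonferroni (0.05/4 = 0.0125): N = 74; power at N = 50 is 0.59.
- Forty co-primary variables with Bonferroni (0.05/40 = 0.00125): N = 110; power at N = 50 is 0.29 per variable.

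**The case against.** **The count is ours and could be too high.** This stands. Step-length variability appears both as a traditional and as an intertrial measure, the unobstructed-walking parameters are not the subject of the stated VR predictions, and the article does not say that every measure is tested separately in each task. Hence the range of 12 to 40. Even if only four predicted effects are counted (compensatory variability, and the onset, spread and accuracy of adjustments), independence gives 1 − 0.975^4 = 9.6%, nearly four times nominal.

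**The measures are correlated.** Also true: they come from the same people and largely the same footfalls, so the independent figures are an upper bound. A reader might infer that a chance finding of VR superiority is more likely than not. The figures do not support that at moderate correlation: at r = 0.5 it is 29% even with 40 variables.

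**The acceptance scores enlarge the problem.** A reader might add the four scales to the total. They are collected in the VR group only, so they yield no between-arm test and cannot produce a VR-superiority result. They are unranked for hypotheses 3 and 4, which is a separate and smaller matter.

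**No time point is fixed.** This too would be overstated. The Objectives and Statistical Analysis sections point to pre versus post, and Table 1 labels T2 as retention. What remains is that T2 sits under the primary outcomes without a rank against T1, and that the text and Table 1 disagree.

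**An analysis plan may settle it.** Multiplicity procedures for secondary families can be left there. Which variable decides the main hypothesis is protocol content, and this article assigns primary status to the whole battery.

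**Conclusion.** The concern holds in this form: the primary gait outcome is a battery with no variable named to decide hypothesis 2, each variable is open to testing at 5%, and the only correction specified works within a single ANOVA. With no true difference between programmes, the chance of at least one result favouring VR is about 16% to 29% at correlation 0.5 and 26% to 64% under independence, against 2.5% for one test. These figures rest on our count of 12 to 40 variables, on equal correlations, and on a superiority claim being made if any one variable is significant. The article does not state such a rule, but it does not exclude it.

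The conflict over assessment times (T1, T2, T3 in the text; T0, T1, T2 in Table 1) is real and leaves the primary contrast less clear than it should be. Because the headline conclusion depends on hypothesis 2, the matter should be settled before data collection.

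**What to change.** Before data collection:
1. Name one gait endpoint and one contrast as primary for hypothesis 2. One candidate already in the plan is the between-arm difference in T0-to-T1 change in the mixed-condition gait adaptability score, once that score is fully defined. Another single variable would serve equally well if the sponsor regards the intertrial or trial-by-trial measures as the heart of the study.
2. Label all other gait variables, and T2, as secondary or exploratory.
3. State that the conclusion on VR superiority rests on the named endpoint only.
4. Reconcile the text and Table 1 on when the primary outcomes are assessed.
5. State separately how the four acceptance scores bear on hypotheses 3 and 4; the choice is the sponsor's.

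The cost is protocol wording. Under the assumptions above, the stated sample size of about 50 still serves for one test. The downside is that no other gait variable can support a confirmatory claim on its own. If the sponsor prefers several co-primary variables, the level must be divided among them and the sample size raised accordingly.

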### Inclusion Criteria and Informed Consent

Participants are independent-living community dwellers aged between 65 and 80 years. They are active older adults with weekly moderate to vigorous physical activity. This study is a part of a broader research program aimed at determining the extent to which new technologies (eg, exergames and XR) can be used to promote healthy aging among active older adults [23,24,65]. Of course, populations of more fragile older adults (eg, older adults who fall) could benefit from an appropriate intervention approach; however, our objective in this study consists, rather, within the framework of a preventive approach of creating the conditions allowing the delay or even avoidance of the occurrence of a first fall.

The exclusion criteria are inability to practice activity at a moderate or vigorous intensity (checked by medical examination supervised by cardiologists), moderate or severe cognitive impairments (ie, a Mini-Mental State Examination score <26 [66]), severe noncorrected visual impairments, and uncontrolled psychiatric disorders.

Every 5 minutes of VR use, the Fast Motion Sickness scale [67], designed to measure cybersickness, will be completed orally by the participant. According to the protocol set up by Keshavarz and Hecht [67], if a participant reaches a score of 15 or more, they will immediately be asked if they wish to stop participating and be told that this will have no harmful consequences for them.

Information about the organization of the gait training programs will be presented to the eligible participants by the principal investigator. Those who are willing to participate will be asked to give informed consent.

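### Limiting the analysis to participants with complete pretests and posttests gives up the protection of randomisation, and the VR arm has an exit offer that the Nordic walking arm lacks

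*Protocol article*

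**What the plan says.** All references are to the protocol article.

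- **Analysis set** (Statistical Analysis): "The analysis will include participants who completed all the pretests and the posttests". The method is repeated measures ANOVA. Adherence is reported separately as an absence rate, with no exclusion threshold.
- **Dropout** (Sample Size): "To test the main hypotheses of this study, 50 participants are required"; then "To compensate for possible dropouts, 5 more participants will be included in each group"; and so "The 2 groups will be composed of 30 participants each". This is the only provision for dropout.
- **VR-only exit offer** (Inclusion Criteria and Informed Consent): cybersickness is scored repeatedly ("Every 5 minutes of VR use, the Fast Motion Sickness scale"), and "if a participant reaches a score of 15 or more, they will immediately be asked if they wish to stop participating". The NW arm has no counterpart, and the article does not describe assessing people after they stop.
- **Acceptance** (VR-HMD Acceptance): "For the VR group only, VR-HMD acceptance before and after use will be assessed using the TAM". There is no comparator for this outcome.
- **Timing** (Table 1): gait adaptability and acceptance are scheduled at T0, T1 (labelled posttests) and T2 (labelled retention). A sentence above the table gives other time points for the primary outcomes; I follow the table and Study Design.

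**The concern.** Randomisation makes the two arms comparable as allocated. A set defined by what happens after allocation no longer has that guarantee. The risk is concrete here because one reason for leaving, cybersickness, can arise only in the VR arm and reflects how well the device is tolerated.

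Two conclusions are exposed:

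- **Gait adaptability.** Hypothesis 2 (greater gains with VR) would be tested on VR participants who stayed to be tested, against NW participants who stayed for possibly different reasons.
- **Acceptance.** Hypotheses 3 and 4 would be judged on VR completers. The rule as written also discards leavers' T0 acceptance answers, although hypothesis 3 concerns acceptance before the programme and those data will already exist.

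An unseen analysis plan could fill a gap, but this is a stated rule.

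**Working it through.** **1. The plan's own figures.** Inputs from Sample Size: f = 0.2, α = 0.05, power 0.80, 50 required, 30 per group. The number of measurements m and their correlation ρ are not given, so I assume them. For the group-by-time interaction with 2 groups:

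- λ = f²·N·m/(1−ρ), with degrees of freedom (m−1) and (N−2)(m−1).
- m = 2, ρ = 0.5, N = 50: λ = 0.04 × 50 × 2 / 0.5 = 8 and power is 0.791; 52 participants reach 0.80.
- m = 3, ρ = 0.4 gives exactly 50.
- Dropout allowance: 10/60 = 16.7%, and 50/(1 − 10/60) = 60, or 30 per group.

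The figures are consistent: about 50 completers keep the planned power. Nothing in the calculation addresses who the completers are.

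**2. Acceptance level (VR arm only).** Let p be the share of the arm lost and g the completer mean minus the mean the leavers would have had. Then

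completer mean − all-randomised mean = p × g.

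The 5 lost of 30 is the plan's allowance. The losses of 2 and 8 and all gaps are assumptions.

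| Lost of 30 | g = 1 | g = 2 | g = 3 |
|---|---|---|---|
| 2 | 0.07 | 0.13 | 0.20 |
| 5 | 0.17 | 0.33 | 0.50 |
| 8 | 0.27 | 0.53 | 0.80 |

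This is bias in a level, so it bears on hypothesis 3. Hypothesis 4 concerns an increase, for which g must be the gap in change. If leavers were lower by the same amount at T0 and T1, the bias in change would be p × 0 = 0.

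**3. Gait comparison (two arms).** With g now in SDs of change,

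bias in VR − NW = p(VR) × g(VR) − p(NW) × g(NW).

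With 5 of 30 lost in each arm, and assumed gaps of 0.5 to 1.0 SD where loss is selective:

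- Selective in VR only: 5/30 × 0.5 = 0.08 to 5/30 × 1.0 = 0.17 SD, favouring VR.
- Equally selective in both arms: 0.
- Selective in NW only: −0.08 to −0.17 SD, favouring NW.

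For scale, f = 0.2 at m = 2, ρ = 0.5 implies a difference in change of 4 × 0.2 = 0.8 SD (the SD of change is √(2 × 0.5) = 1). A bias of 0.08 to 0.17 SD is about 10% to 21% of that. In the VR-only case with 25 analysed per arm, the standard error is √(2/25) = 0.283, and the two-sided rejection rate under no true difference rises from 0.05 to about 0.06 to 0.09 (normal approximation).

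**The case against.** **Exclusion follows missed tests, not stopping VR.** A reader might infer that anyone who stops VR leaves the analysis. The text does not say so: someone who stops or skips sessions but completes the tests stays in, and a high cybersickness score leads to a question, not to withdrawal. This stands. What remains is that the offer is to stop participating, with no later assessment described, so missed posttests are plausible but inferred.

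**The gait bias need not favour VR.** That reading is tempting, but it requires VR leavers to have gained less and NW losses to be fewer or less selective. The article shows neither. NW takes place outdoors on uneven terrain and may also lose people selectively, and the plan allows 5 losses in each arm. This stands, and the gait direction is conditional. The introduction does say that attitudes toward the technology may influence its effectiveness, which makes smaller gains among VR leavers credible, but that is not evidence.

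**Loss of people missing only T2.** A reader might infer that they are dropped altogether. Table 1 labels only T1 as posttests, and the planned comparison is before against after the intervention, so the text does not establish this.

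**A mixed model is not a cure.** Someone with only T0 data adds almost nothing on change, and the model assumes missingness is explained by observed data, which loss through intolerance may violate. This stands and shapes the remedy.

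None of these points supports restricting the primary analysis to completers.

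**Conclusion.** The completers rule should not define the primary analysis. It gives up the protection of randomisation in a trial where one exit offer exists in one arm only, and over-recruiting by 5 per group restores numbers without restoring comparability.

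- **Acceptance level:** probably overstated, because leavers are likely to be less favourable and no comparator offsets the selection. With 5 of 30 lost and an assumed gap of 1 to 3 points, the overstatement is 0.17 to 0.50 points. This figure does not carry over to the increase in acceptance.
- **Gait adaptability:** bias is possible in either direction and is zero if losses are equal and equally selective. It favours VR only under the conditions stated above.

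The true size cannot be computed, because the article gives no expected loss or cybersickness rate by arm. The illustrations use 30 per group from Sample Size; the abstract's total of 40 conflicts with this and needs reconciling separately. The case for change therefore rests on principle and on the low cost of the remedy, not on a demonstrated size.

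**What to change.** Before data collection starts, since outcomes not collected cannot be recovered:

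1. Define the primary analysis as all randomised participants in their allocated arm, using all available T0, T1 and T2 observations in a linear mixed model with a participant random effect. For acceptance, use the same approach within the VR arm and keep T0 answers for all VR participants.
2. Continue to invite people who stop training to the scheduled T1 and T2 assessments, including the acceptance questionnaire in the VR arm. This step does most to reduce bias. The offer to stop after a high cybersickness score is unaffected, and attendance remains voluntary.
3. Report losses and reasons by arm.
4. Add a simple sensitivity analysis for informative dropout: shift the assumed outcomes of leavers downwards by a range of amounts, separately by arm, and state at what shift the conclusion changes.
5. Keep the completers analysis as a sensitivity analysis.

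The cost is revised wording and slightly more analysis work, with no new visits or participants. The estimated effect may be smaller than among completers. In return, if outcomes were obtained from all 60, power would be about 0.86 rather than 0.79 with 50 completers (m = 2, ρ = 0.5 assumed, same effect size).
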